## Abstract

Background: The rapid aging of China’s population poses significant challenges, particularly in public health and medical services. Frailty, a reversible geriatric syndrome, is a critical intervention target for disability prevention among older adults. Objective: We hypothesize that both intervention groups will demonstrate significant improvements in Short Physical Performance Battery (SPPB) scores compared to the control group, and that these improvements will be accompanied by parallel reductions in inflammatory markers and beneficial alterations in the gut microbiota. Methods: The MultIfaceted NUtrition inTervention for frail Elderly (MINUTE) trial is a randomized, parallel-group controlled trial. In Beijing, China, 315 frail older adults were recruited and randomly assigned to 3 groups: a control group receiving routine community health management only, multifaceted nutrition intervention group, and a multifaceted nutrition and exercise combined intervention group, each comprising 105 participants. The study consists of a three-month intervention period followed by a nine-month follow-up. During the three-month intervention period, the control group receives routine community health management, while the multifaceted nutrition intervention group receives daily dietary guidance, personalized nutrition consultations, and health education. Additionally, the combined intervention group receives exercise interventions in addition to the nutritional components. After the three-month intervention, all three groups will be followed up for nine months to assess the sustainability of the study. Results: The primary outcomes are the changes in the SPPB scores. The secondary outcomes include frailty scores, intrinsic capacity, malnutrition risk, frailty recovery rates, serum differential metabolites, inflammatory factors, and gut microbiota changes. This study aims to establish a scalable and sustainable pathway for frailty prevention among community-dwelling older adults in China and provide valuable insights to inform strategies for healthy aging. Trial registration: This study is conducted in accordance with the Declaration of Helsinki and approved by the Peking University Institutional Review Board (IRB00001052-23178) on February 3, 2024, with all amendments subject to prior review and approval. Informed consent is obtained from participants, and findings will be disseminated through peer-reviewed publications, conference presentations, and summaries for school staff and participants. ClinicalTrials.gov (NCT06547593) registered 30 July 2024.

## 1. Introduction

The global elderly population is undergoing rapid expansion, with the age group of 65 and older experiencing the most pronounced growth. China’s population is aging rapidly, and this demographic shift is becoming increasingly prevalent across the nation [1,2]. Research findings suggest that the risks of falls, disability, delirium, hospitalization, and premature mortality among the elderly are progressively rising in tandem with the aging process [3]. This trend exacerbates the burden on caregivers and healthcare systems, thereby intensifying the challenges of an aging society [4,5]. By 2050, projections indicate that individuals aged 65 and older will comprise one-third of the total population [6]. The swift demographic shift toward an aging population in China [7], characterized by a substantial base of elderly individuals, is rapid and outpacing the country’s current level of socioeconomic development [8]. This demographic transition poses significant challenges to multiple sectors of Chinese society [9], particularly to public health and medical services. Consequently, addressing the challenges associated with an aging population has been prioritized as a national policy in China.

The overall health status of China’s elderly population is a cause for concern. Approximately 44 million older adults experience partial or complete disability, which places a substantial strain on their families [10]. This not only casts a long shadow over their own lives [11] but also places a significant burden on their families and society [12,13]. Disability has become a pressing public health issue that demands the attention of the entire nation [14].

Frailty, a geriatric syndrome marked by heightened vulnerability to stressors, reflects a state of reduced physiological reserve and impaired function across multiple organ systems, resulting in increased dependency and mortality [15,16]. A study based on data from 62 countries indicates that the prevalence of frailty is 24%, while the prevalence of pre-frailty can be as high as 49% [17]. Frailty serves as a critical intervention target for disability, as it is reversible. The screening and intervention of frailty are essential for preventing disability among older adults and promoting their vitality. Addressing frailty is crucial for enhancing the quality of life and independence of the elderly, thereby alleviating the societal burden associated with an aging population [18,19].

Frailty is increasingly recognized in geriatric medicine, with more and more guidelines and expert consensus being developed. A growing number of frailty intervention studies are also being conducted. Existing frailty intervention studies encompass physical activity [20,21], nutritional supplementation [22], cognitive training [23,24], comprehensive geriatric assessments [25], physical activity combined with nutritional supplementation [22], and multicomponent interventions (e.g., physical activity, nutritional supplementation, educational activities, group dining, personalized nutrition advice, and social support) [26]. A growing body of evidence has demonstrated the potential of these interventions in managing frailty. Physical exercise, particularly resistance and multicomponent training, has consistently been shown to improve muscle strength, gait speed, and physical performance, which are core components of the frailty phenotype [20,21]. However, the long-term sustainability of these benefits often requires ongoing exercise commitment, and adherence can be challenging [27]. Nutritional supplementation, primarily focusing on protein and vitamin D, has demonstrated efficacy in addressing sarcopenia—a key element of frailty—and reducing malnutrition risk [28]. Nevertheless, the effects of isolated nutritional supplementation on broader frailty metrics are often modest, suggesting that simply addressing nutrient deficits may be insufficient [29]. Multicomponent interventions, which integrate physical activity, nutritional support, and other elements like cognitive training, represent a more holistic approach. Landmark trials, such as the SPRINTT project, have shown that such integrated interventions can significantly reduce the risk of mobility disability in frail older adults [22]. Similarly, the VIVIFRAIL study demonstrated that a tailored multicomponent exercise program improved functional capacity in frail, pre-frail, and robust older adults [30]. Despite their promise, these comprehensive approaches often face challenges in real-world implementation, including complexity, high resource demands, and limited evidence of scalability in diverse community settings, particularly within the specific socio-cultural context of China [31].

However, current research has several limitations when considered for application in China. Firstly, most studies remain limited to the guideline level, significantly lagging in practical application, failing to address the individualized needs of the elderly, overlooking the considerations of multiple stakeholders, and lacking clear, actionable, and feasible practical pathways. Secondly, existing guidelines predominantly focus on foreign contexts and do not align with Chinese characteristics, lacking research evidence specifically tailored to the Chinese population. There is also a dearth of research on the prevention and management of frailty among the elderly in community settings. Therefore, there is a pressing need to conduct a multidimensional nutritional intervention study on frailty among older adults in China. Against this backdrop, we propose the initiation of the MultIfaceted NUtrition inTervention for frail Elderly (MINUTE) project, which aims to bridge the aforementioned gaps and provide a valuable pathway for healthy aging.

## 2. Methods

### 2.1. Aims

The primary aim of the MINUTE trial is to evaluate the effects of a multifaceted nutrition intervention and a combined nutrition and exercise intervention on physical performance (SPPB score) among frail older adults.

Primary hypotheses: We hypothesize that (1) after the 3-month intervention, both the multifaceted nutrition intervention group and the combined intervention group will show a greater improvement in SPPB score compared to the control group. (2) The improvements in physical performance and frailty in the intervention groups will be mediated by concurrent reductions in systemic inflammation and beneficial alterations in the gut microbiota composition.

Secondary hypotheses: We further hypothesize that the multifaceted nutrition and exercise combined intervention will be superior to the nutrition-only intervention in improving physical performance.

### 2.2. Study Design

The MINUTE trial is a randomized, parallel-group, controlled study involving a total of 315 participants. Participants will be randomly assigned to one of three groups: a control group that will receive routine community health management and serve as the reference for comparing the effectiveness of the active interventions, a multifaceted nutrition intervention group, or a multifaceted nutrition and exercise combined intervention group. Each group will include 105 participants and will receive a different intervention over a 3-month period, followed by a 9-month follow-up. Upon study completion, between-group comparisons will be conducted to evaluate the differential effects of the interventions. Figure 1 illustrates the study flowchart from participant inclusion through the follow-up phase. Figure 2 (graphical abstract) provides a detailed overview of the study population, design, and interventions. The trial has been registered on ClinicalTrials.gov (Identifier: NCT06547593).

### 2.3. Recruitment of Participants

Participants will be recruited from the senior community. We will collaborate with the Community Health Service Center to disseminate recruitment information through community physicians and neighborhood committees. Recruitment will be conducted in several stages to ensure a thorough and systematic approach:(1)Initial contact and information dissemination: Community physicians and neighborhood committees will identify potential participants who meet the basic age criteria (aged 65 years or older). They will provide these individuals with detailed information about the study, including its purpose, procedures, risks, and benefits. This information will be delivered through flyers, community announcements, and face-to-face consultations.(2)Screening and pre-selection: Potential participants will be invited to attend a preliminary screening session at the Community Health Service Center. During this session, community physicians will conduct a brief health assessment and administer the FRAIL scale to determine the frailty status. Individuals who are assessed as frail by the FRAIL scale will be considered for further evaluation.(3)Informed consent and detailed assessment: Eligible individuals will be provided with a detailed explanation of the study procedures and will be asked to provide written informed consent. Following consent, a comprehensive baseline assessment will be conducted by trained healthcare professionals. This assessment includes a review of medical history, physical examination, and evaluation of functional and mental health status.

Inclusion criteria include the following:(1)Assessed as frailty by the FRAIL scale. The FRAIL scale is a simple 5-item screening tool where frailty is defined as meeting 3 or more of the following criteria: fatigue, resistance (inability to climb one flight of stairs), ambulation (inability to walk 100 m), illnesses (≥5 comorbidities), and loss of weight (>5% in the past year).(2)Aged 65 years or older.(3)Able to provide written informed consent, after receiving a detailed explanation of the study purpose, procedures, risks, and benefits.

Exclusion criteria include the following:(1)Major comorbidities: History of major comorbidities (e.g., stroke, myocardial infarction, active cancer, or severe cardiocerebrovascular disease) that may confound study results or pose risks to participants.(2)Significant functional impairments: Participants with disability, dementia, severe visual or hearing impairments, or physical activity impairment will be excluded. These impairments will be assessed through standardized functional tests (e.g., Mini-Mental State Examination for cognitive function, visual acuity tests, and hearing assessments) and physical performance tests (e.g., gait speed and balance tests). The exclusion will be based on the potential for these impairments to limit participants’ ability to complete the study protocol or accurately report outcomes.(3)Moderate to severe mental health conditions: Participants with moderate to severe anxiety or depression will be excluded. Mental health status will be evaluated using validated screening tools (e.g., the Geriatric Depression Scale and the State-Trait Anxiety Inventory). The exclusion will be based on the potential for these conditions to affect participants’ ability to comply with the study protocol or accurately report outcomes.

### 2.4. Randomization, Allocation Concealment, and Blinding

After providing consent and completing the baseline assessment, participants will formally enter the study and be randomly assigned to the control group, the multifaceted nutritional intervention group, or the multifaceted nutrition and exercise combined intervention. The randomization sequence is generated by a statistician from Peking University using computer-generated random numbers. Randomization will be performed in a 1:1:1 ratio using computer-generated random numbers. There will be no blocking or stratification. The allocation will be concealed through central randomization performed by an investigator who is not involved in the assessment or recruitment, and the recruitment personnel will not have access to the group assignment tables. Given the nature of the behavioral interventions, it is not possible to blind the participants or the staff delivering the interventions (nutritionists and exercise specialists). Therefore, this is an assessor-blinded trial. Outcome assessors (staff responsible for administering the physical and cognitive tests) and data analysts will be blinded to group assignment throughout the trial. Participants will be instructed not to reveal their intervention allocation to the outcome assessors. The blinding status of the assessors will be evaluated at the end of the study by asking them to guess the group assignment of the participants.

## 3. Intervention

Table 1 outlines the intervention content for each group.

### 3.1. Control Group

The control group will receive routine community health management only, which represents the standard level of care currently available for frail older adults in the community. This includes monthly health education lectures on general topics (e.g., chronic disease prevention), provision of standard health education materials, and access to basic health counseling services. Critically, the control group will not receive the study’s active intervention components, such as the personalized nutritional consultations, anti-inflammatory diet guidance, provision of protein powder and whole grains, structured exercise guidance, or the intensive bi-weekly health education lectures specific to frailty and malnutrition that are delivered to the intervention groups.

### 3.2. Multifaceted Nutrition Intervention

In this group, a three-month multifaceted nutrition intervention will be conducted. All nutritional interventions and recommendations will be provided to participants based on professional discussions and reviews by nutrition experts from the School of Public Health at Peking University. The specific content is as follows:

(1) Daily dietary guidance: Participants will receive an anti-inflammatory dietary menu (Supplementary Table S1) designed based on the Chinese Dietary Guidelines for the Elderly (2022 Edition) and principles from the Dietary Inflammatory Index [32,33]. The diet emphasizes the intake of fruits, vegetables, whole grains, nuts, and fatty fish while reducing refined carbohydrates and saturated fats. Additionally, we will provide participants with a daily nutritional supplement containing 10 g of whey protein to address the high prevalence of sarcopenia in frail elders and support muscle protein synthesis [34], along with 50 g of whole grains to increase dietary fiber and phytochemical intake, which are associated with improved gut microbiota and reduced systemic inflammation [35,36].

(2) Personalized nutritional intervention: In response to specific health issues and diseases, we have established fixed consultation times at community hospitals, allowing elderly individuals to seek advice at designated intervals if they have health-related needs. Furthermore, we will offer on-demand online consultations with registered dietitians to promptly address the nutrition and health concerns of the elderly.

(3) Health education: Every two weeks, nutrition and health knowledge lectures (Table 2) will be conducted for elderly family caregivers and the elderly themselves, covering topics such as chronic diseases, malnutrition, and frailty.

### 3.3. Multifaceted Nutrition and Exercise Combined Intervention

In addition to the aforementioned nutritional measures, exercise interventions will also be included, guided by experts from the Physical Education Department at Peking University. We will provide an exercise intervention manual and a wheel diagram, guiding the elderly to follow a weekly schedule with three days dedicated to resistance exercise sessions and four days for walking, combining resistance and aerobic exercises in a scientifically alternated manner. The weekly resistance exercise program, conducted three times a week, includes eight exercise sessions: twisting towels, lifting water bottles, sit-to-stand training, obstacle crossing, walking in an 8-shape pattern, leg extensions, arm extensions, and seated straight leg raises. These sessions provide comprehensive physical training guidance for the elderly, with details available in Figure 3 and the exercise intervention manual.

To ensure the correctness and safety of the exercises, and to enhance adherence, we will implement a multifaceted support system rather than relying solely on unsupervised self-practice. This includes the following:(1)Initial supervised instruction: Prior to starting the home-based program, each participant will attend a one-on-one or small-group session with a trained exercise specialist. During this session, the specialist will demonstrate each exercise, ensure the participant can perform it with correct form, and provide personalized feedback.(2)Structured guidance materials: Participants will receive a detailed, illustrated exercise manual and a training wheel chart (Figure 3) that clearly outlines the weekly schedule, sets, and repetitions, making the program easy to follow at home.(3)Ongoing remote support: Participants will have weekly access to an exercise specialist via an online platform or telephone to ask questions, report difficulties, and receive motivational support.(4)Adherence monitoring: Participants will be asked to maintain a simple exercise diary to log their completed sessions. This will be reviewed weekly by the research team to monitor adherence and provide timely reminders if needed.(5)Integration with community healthcare: To leverage the existing community healthcare network, community hospitals and family physicians will be engaged to provide ongoing supervision. During their routine weekly interactions or health consultations, they will specifically inquire about the participants’ exercise progress, record their adherence, and offer encouragement. This integrates the intervention into the participants’ regular healthcare, providing an additional layer of personal contact and accountability.

### 3.4. Quality Control of the Intervention

(1)To ensure the fidelity and successful implementation of the intervention while prioritizing the safety of the elderly, we will mobilize the involvement of multiple institutions. Nutrition experts offer personalized consultation and guidance on dietary needs, while exercise specialists provide tailored recommendations at varying intensity levels. Community hospitals contribute by offering examination venues and equipment, and family doctors are tasked with ensuring the safety of the elderly. Additionally, staff from senior living communities or care centers assist in the project’s execution, and the elderly actively engage in feedback and communication, sharing their thoughts and experiences.(2)Three manuals (“Nutrition Intervention Manual for Older Adults”, “the Staff Manual for the Nutrition Intervention Program for Older Adults”, and “Exercise Intervention Manual”) will be used to implement and manage this complex intervention. The manuals detail the responsibilities of study personnel at each stage of the project. The manuals also describe in detail the work processes for implementing each component of the intervention, i.e., who, when, how, and to what extent specific intervention elements are to be delivered.(3)Throughout the implementation process, project executors will conduct regular interviews and exchanges with the elderly, promptly conveying their thoughts and feedback to the project leaders. Periodic meetings will be held to consolidate the opinions of all stakeholders involved in the project, allowing for the continuous optimization and improvement of any emerging issues.(4)We will employ a comprehensive set of measures to collect process indicators and ensure adherence to the intervention, as follows:

Participant activity diary: Records of frail individuals completing nutritional or exercise sessions as prescribed are maintained.Satisfaction survey: Frail older adults will be asked to rate their satisfaction with the weekly interventions using smiley faces.Online check-ins: Daily check-in frequency and time periods are recorded by designated personnel, detailing the specific daily meals and exercise routines.Lecture logs: Records of attendance at each online and offline lecture are maintained, forming a participant log.Urinary sodium monitoring: Urine samples from frail elderly individuals will be collected before and after the intervention to monitor urinary sodium levels, assessing dietary adherence.

## 4. Outcomes

Table 3 describes the study outcomes, including when and how the study outcomes will be evaluated. Baseline measurements will be conducted for all three groups. Follow-up measurements will be conducted at 3 months (end of intervention), 6 months, and 12 months (end of follow-up) after the baseline measurement. The primary and secondary outcomes will be assessed by comparing changes from baseline within and between groups.

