### 4.1. Primary Outcome

The primary outcome is physical performance, assessed by the change in the Short Physical Performance Battery total score from baseline to the three-month assessment (time point). The SPPB is a well-validated tool ranging from 0 (worst) to 12 (best), assessing balance, gait speed, and lower limb strength. The change will be analyzed as a continuous variable, and the between-group difference will be expressed as the mean difference with a 95% confidence interval.

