### 4.6. Statistical Analyses

This study will employ the Intention-to-Treat (ITT) and Per-Protocol (PP) analysis sets to ensure that all randomized study subjects remain in their assigned groups. The Intention-to-Treat population will include all randomized participants, analyzed according to their assigned group. The Per-Protocol population will include only those participants who completed the intervention as prescribed and had no major protocol deviations. For missing quantitative data, the last observation carried forward method will be used. When the results of the ITT and PP analyses are consistent, the ITT results will be presented. When the results differ, the differences will be discussed. The variables will be analyzed using SPSS V.23.0 software. All statistical tests will be two-sided at the 5% level of significance. Continuous variables with a normal distribution will be shown as the mean and SD and those with an abnormal distribution will be presented as the median and IQR. Categorical variables will be expressed as a percentage or constituent ratio. Baseline characteristics will be presented for each group using descriptive statistics (means and standard deviations for normally distributed continuous data, medians and interquartile ranges for non-normally distributed data, and frequencies and percentages for categorical data). Mixed-model repeated-measures analysis of variance with adjustment for baseline characteristics will be performed for different measurement time points between groups, and interaction between groups and measurement time. For continuous outcomes, we will report the pre- and post-intervention means for the intervention and control groups, as well as the model-adjusted mean differences between groups. For binary outcomes, we will report the pre- and post-intervention percentages for the intervention and control groups, along with the adjusted odds ratios (ORs) between groups. The 95% confidence intervals (CIs) and associated *p*-values will be calculated. We will use nontargeted metabolomics methods to examine the changes in serum differential metabolites in each group before and after the intervention and explore the mechanism of intervention. We will use 16S rRNA gene sequencing to detect changes in gut microbiota and differential bacterial genera among groups. To address the second primary hypothesis regarding the potential mechanisms, correlation analyses (Spearman’s or Pearson’s correlation) and mediation analysis will be performed to examine the relationships between changes in clinical outcomes (SPPB score and frailty) and changes in biomarker levels (inflammatory markers and microbial abundance). Subgroup analyses will be conducted to investigate whether the effects of the intervention vary across different demographic and clinical subgroups.

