Measurements	Time Points				Instrument/Method of Assessment	Outcome Variables
	Baseline	3 Months	6 Months	12 Months		
Physical examination						
Height	Yes	Yes	Yes	Yes	Stadiometer	BMI
Weight	Yes	Yes	Yes	Yes	Lever scale	
Waist/Calf circumference	Yes	Yes	Yes	Yes	Tape	Waist/Calf circumference
Sebum	Yes	Yes	Yes	Yes	Sebaceous pliers	Body fat percentage
Body composition analysis	Yes	Yes	Yes	Yes	Body composition analyzer/bioelectrical impedance analysis technique	Body fat mass, body fat percentage, defatted body weight, muscle mass, body water, protein, inorganic salts, and other data
(Strength of one’s) Grip	Yes	Yes	Yes	Yes	Grip strength meter/adjust for palm size, measure with index finger second joint at a right angle, maximum effort	Grip strength measurements
Simple Physical Performance Based Assessment (SPPB)						
Balance testing	Yes	Yes	Yes	Yes	Timekeeping device/includes balancing in 3 different difficulty positions: feet together, half tandem standing, and tandem standing.	Test scores
3 or 4 meter pace test	Yes	Yes	Yes	Yes	Timekeeping device/walk at maximum speed. Record the shortest of two trials.	Test scores
Timed Sit-Stand Test	Yes	Yes	Yes	Yes	Timekeeping device/assess lower limb strength in elders by timing 5 rapid sit-to-stand cycles with a stopwatch.	Test scores
Frailty status						
Fried Frailty Phenotype	Yes	Yes	Yes	Yes	Scale questionnaire	Scale score
Tilburg Frailty Indicator	Yes	Yes	Yes	Yes	Scale questionnaire	Scale score
Frailty trajectories	Yes	Yes	Yes	Yes	Changes in frailty trajectories before and after the intervention, as measured by the Frailty Index	
Frailty recovery rates	Yes	Yes	Yes	Yes	Difference in frailty scores before and after intervention	
Nutritional status						
Malnutrition risk assessment	Yes	Yes	Yes	Yes	Scale questionnaire	Scale score
Nutritional literacy assessment for the elderly	Yes	Yes	Yes	Yes	Scale questionnaire	Scale score
Metabolomics						
Serum protein	Yes	Yes		Yes	Physiological and biochemical tests	Serum total protein, albumin, and transferrin
Urine 8-hydroxyguanosine (8-oxo-Gsn)	Yes	Yes		Yes	Physiological and biochemical tests	
Serum inflammatory factors	Yes	Yes		Yes	Physiological and biochemical tests	
Changes in serum differential metabolites	Yes	Yes			Utilize nontargeted metabolomics to assess serum metabolite changes pre- and post-intervention, elucidating the intervention’s mechanism	
Microbiota						

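### Section 4 lists within-group change as a way of assessing every outcome without calling it descriptive, and serum metabolomics is given only a per-arm before/after analysis

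*Protocol article*

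**What the plan says.** Section 4 (Outcomes) sets one rule for all outcomes: "The primary and secondary outcomes will be assessed by comparing changes from baseline within and between groups". Section 4.6 adds "All statistical tests will be two-sided at the 5% level of significance" and exempts no comparison as descriptive.

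Other sections point to the randomised comparison:

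- Section 2.1: the primary hypothesis is that each intervention group "will show a greater improvement in SPPB score compared to the control group".
- Section 2.2: "between-group comparisons will be conducted to evaluate the differential effects of the interventions".
- Section 4.1, for SPPB change at 3 months: "the between-group difference will be expressed as the mean difference with a 95% confidence interval".
- Section 4.6: the mixed model "will be performed for different measurement time points between groups, and interaction between groups and measurement time". Continuous outcomes get pre and post means "as well as the model-adjusted mean differences between groups", and binary outcomes get pre and post percentages with adjusted between-group odds ratios.

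Serum metabolites are treated differently. Section 4.2, item (11), and section 4.6 describe looking at how they change from before to after in each group, in order to explain the intervention's mechanism. Neither place names a contrast between groups. For gut microbiota, by contrast, both sections look for differences among groups.

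Table 3 also uses before/after terms. Frailty trajectories are "Changes in frailty trajectories before and after the intervention, as measured by the Frailty Index", and frailty recovery is a before/after difference in frailty scores. Section 4.2, item (4), defines recovery differently, as the proportion of participants who move out of the frail state.

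**The concern.** A before/after comparison in one arm shows whether that arm changed. It does not show whether the intervention caused the change; only the comparison with the concurrent randomised control does. Finding a significant change in an intervention arm and none in control is not a test of the difference between them.

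A shift common to all arms is plausible here. Participants are enrolled because they screen as frail, they repeat timed tests and questionnaires at up to four visits, and controls also receive monthly lectures and counselling. For serum metabolites, season or sample handling could move all arms together as well. The document gives no size for any such shift.

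If section 4 is read literally, an outcome with no between-group difference could be reported as improved in an intervention arm, and that report would still follow the protocol. For metabolomics no literal reading is needed, because per-arm change is the only analysis stated. A metabolite that moved equally in all three arms would be listed as changed in the intervention arms and could be offered as part of the mechanism.

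**Working it through.** **Reading the sections together.** The plan gives no figure of its own on this point, so the main check is textual.

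| Outcome | Between-group contrast stated? | Where |
|---|---|---|
| SPPB at 3 months | Yes | 2.1, 4.1, 4.6 |
| Other continuous outcomes | Yes, in general terms | 4.6 |
| Binary outcomes, including recovery as a proportion | Yes, odds ratio | 4.2(4), 4.6 |
| Gut microbiota | Yes, among groups | 4.2(12), 4.6 |
| Serum metabolites | Not in their own description; change in each group only | 4.2(11), 4.6 |

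The correlation and mediation analyses in section 4.6 do not close the last gap. The biomarkers they name are inflammatory markers and microbial abundance, not metabolites.

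**Illustration of what a within-arm test does under shared drift.** SPPB is used because it is the only outcome for which the document gives an SD.

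Inputs:
- SD of change 2.5 (section 4.5).
- 105 per arm with 10% loss (section 4.5): 105 × 0.9 = 94.5, taken as 95.
- Two-sided 5% level (section 4.6).
- Assumed, not in the document: no intervention effect, normally distributed changes, and the same true drift δ in all three arms.

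Steps:
1. Standard error of one arm's mean change: 2.5/√95 = 0.2565.
2. Smallest significant within-arm change: t(94) = 1.986, and 1.986 × 0.2565 = 0.51 points.
3. Smallest significant between-arm difference: 0.2565 × √2 = 0.3627, t(188) = 1.973, and 1.973 × 0.3627 = 0.72 points.
4. Probability p that one arm shows a significant gain: the upper tail beyond 1.986 of a noncentral t with 94 df and noncentrality δ/0.2565.
5. At least one of the two intervention arms significant: 1 − (1 − p)².
6. At least one intervention arm significant and control not: [1 − (1 − p)²](1 − p).

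| δ (assumed) | δ/0.2565 | p | Step 5 | Step 6 |
|---|---|---|---|---|
| 0 | 0 | 0.025 | 0.049 | 0.048 |
| 0.3 | 1.17 | 0.211 | 0.378 | 0.298 |
| 0.5 | 1.95 | 0.488 | 0.738 | 0.378 |
| 0.7 | 2.73 | 0.771 | 0.947 | 0.217 |

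A between-group test is unaffected by δ, because a shared drift cancels in the difference. Each contrast keeps its 5% level in every row.

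**The case against.** The strongest reply is that section 4 contains one loose sentence and the operative analysis is in section 4.6. That section gives between-group differences for continuous outcomes and odds ratios for binary ones, without limiting them to SPPB. Its pre and post means are descriptive, and it names no paired or within-arm test for the clinical outcomes. The 5% statement sets a level and creates no tests. Nowhere does the document say that a within-arm change establishes efficacy. This stands, and it limits the point for those outcomes to an inconsistency.

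Two further replies also stand in part. The Table 3 entries sit in the column for instrument or method of assessment, so they describe measurement more than inference; what remains is that the recovery entry does not match section 4.2, item (4). The calculation uses SPPB, the best-protected outcome, and its result depends on an assumed drift. Selection on the FRAIL scale at screening, with a separate baseline assessment after consent, makes regression to the mean in SPPB an indirect argument.

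It could also be said that metabolite levels are continuous and so fall under the general sentence in section 4.6. That reading is possible. However, the sentence written specifically for metabolites says change in each group, while the next one, for microbiota, names a comparison among groups. The text therefore does not settle it.

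Leaving detail to an analysis plan does not answer the point. The objection is to what the article states, not to something it omits.

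**Conclusion.** The point holds in a limited form. Section 4 places within-group change beside the between-group comparison for all primary and secondary outcomes and does not mark it as descriptive. For the clinical outcomes this conflicts with sections 2.1, 2.2, 4.1 and 4.6 and should be tidied. For serum metabolomics it is a substantive defect, because the only analysis stated for it cannot separate an intervention effect from a shift shared by all arms, yet it is meant to explain mechanism.

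A reader might infer more: that no secondary outcome is protected by a between-group comparison, that the plan adds three within-arm 5% tests per outcome and visit, or that the primary analysis has an inflated error rate. The documents do not support these. Section 4.6 covers continuous and binary outcomes generally, no within-arm test is named for the clinical outcomes, and the primary effect is tied to control.

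The range of 38% to 95% shows the mechanism only. It rests on an SD of 2.5, 95 completers per arm, no intervention effect and an assumed drift of 0.3 to 0.7 SPPB points. With zero drift it is 5%. It is not a forecast for the primary result, and the document offers no inputs for a corresponding figure for metabolites.

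**What to change.** 1. In sections 4 and 4.6, state that conclusions about intervention effects on all primary and secondary outcomes rest only on between-group differences in change from baseline, adjusted for the baseline value. Within-group changes are given descriptively with 95% confidence intervals.
2. In section 4.2, item (11), and section 4.6, specify a between-group contrast in change for serum metabolites, each intervention arm against control, and base any statement about mechanism on it.
3. In Table 3, replace the frailty recovery entry with the proportion defined in section 4.2, item (4), compared between groups.

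The cost is wording only: no new data and no change in sample size. The one loss is that per-arm before/after p-values can no longer support a claim of effect.
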